### Measurements

Table 1 illustrates the trial schedule of visits and assessments. A range of validated clinical and physical health measures will be administered at different points throughout the trial period. Clinical measures will be administered by clinical trial staff, whom the clinical trial research manager will supervise. These staff are experienced mental health clinicians trained to administer these measures. Depending on participants' preferences, clinical measures will be administered in the clinic or at the participant's residence.

**Table 1 tab01:** Schedule of trial visits and assessments

Visit	0 (Screening)	1 (Baseline)	2	3	4	5	6	7
							
Week		0 (Baseline)	2	4	6	8	10	12
Study medication period (12 weeks)								
Screening and consent								
Assessment of current medication	x	x	x	x	x	x	x	x
Informed consent	x							
Ongoing capacity	x	x	x	x	x	x	x	x
Inclusion/exclusion criteria	x							
Urine pregnancy test (females only)	x							
Investigational product supply (fortnightly)		x	x	x	x	x	x	
Safety^a^								
Dropouts								x
Adverse events		x	x	x	x	x	x	x
SAFTEE-SI		x	x	x	x	x	x	x
Efficacy^a^								
Height		x						
Body weight		x		x		x		x
Waist circumference, waist-to-hip ratio		x		x		x		x
Heart rate		x		x		x		x
Blood pressure		x		x		x		x
HDL, LDL, triglycerides, total cholesterol		x						x
HbA1c		x						x
NAFLD, FIB-4		x						x
PANSS total and subscale scores		x		x		x		x
GAF		x						x
SIMPAQ		x						x
AQoL-4D		x						x
CGI		x						x
TOPF		x						x
BACS verbal memory and learning		x						x
BACS digit sequencing task		x						x
BACS symbol coding task		x						x
BASC semantic and letter fluency		x						x
HRSA		x						x
CDSS		x						x
TMT		x						x
FCI		x						x
AUDIT		x						x
PSQI		x						x
Other^a^								
Trial medication compliance			x	x	x	x	x	x
Blood (other) – FBC (WCC, Neutrophils, lymphocytes), ELFT, clozapine/ norclozapine levels		x			x			x
Blood (other) – CBD and CBD metabolites (7-COOH-CBD, 6-OH-CBD, 7-OH-CBD)		x						x
Blood (other) – THC and THC metabolites		x						x
DNA saliva sample^b^		x						

SAFTEE-SI, Systematic Assessment for Treatment Emergent Events – Systematic Inquiry; HDL, high-density lipoprotein; LDL, low-density lipoprotein; HbA1c, glycated haemoglobin; ELFT, electrolyte and liver function tests; NAFLD, non-alcoholic fatty liver disease; FIB-4, fibrosis-4; PANSS, Positive and Negative Syndrome Scale; GAF, Global Assessment of Function; SIMPAQ, Simple Physical Activity Questionnaire; AQoL, Assessment of Quality of Life; CGI, Clinical Global Impression; TOPF, Test of Premorbid Function; BACS, Brief Assessment of Cognition in Schizophrenia; HRSA, Hamilton Rating Scale for Anxiety; CDSS, Calgary Depression Scale for Schizophrenia; TMT, trail making test; FCI, Food Craving Inventory; AUDIT, Alcohol Use Disorders Identification Test; PSQI, Pittsburgh Sleep Quality Index; FBC, full blood count; WCC, white cell count; CBD, cannabidiol; THC, tetrahydrocannabinol.

a. Assessment schedule may vary by plus or minus 5 days for operational convenience.

b. Providing a saliva sample is optional for participants and will be used to explore the presence of known correlates of clozapine and obesity, including variants in genes such as *LEP* and *HTR2C*.

### Efficacy measures

The PANSS positive score will be the primary outcome.^26^ Secondary outcome measures will include the following:
PANSS total and other subscale scores (negative scale and general psychopathology scale);^26^Global Assessment of Function: a numeric scale from 1 to 100 used by clinicians to subjectively rate participants' social, occupational and psychological functioning;^27^Simple Physical Activity Questionnaire: a five-item instrument designed to measure physical activity and sedentary behaviour in various populations, including clinical samples with high levels of sedentary behaviour;^28^Assessment of Quality of Life 4 Dimensions: a 12-item instrument that captures four dimensions of quality of life, comprising independent living, mental health, relationships and senses;^29^Clinical Global Impression: a measure of symptom severity, treatment response and treatment efficacy in treatment studies of people with schizophrenia;^30^Test of Premorbid Functioning: a measure of pre-injury IQ and memory ability;^31^Brief Assessment of Cognition in Schizophrenia (BACS) Verbal Memory and Learning: a measure of episodic verbal learning memory;^32^BACS digit sequencing task: a measure of working memory;^32^BACS symbol coding task: a measure of non-verbal functions such as attention, flexibility, speed of processing and abstract reasoning;^32^BACS semantic and letter fluency: a verbal fluency test that measures spontaneous production of words that belong to the same category or begin with the same letter;^32^Hamilton Rating Scale for Anxiety: a measure of anxiety symptom severity;^33^Calgary Depression Scale for Schizophrenia: a nine-item measure of depression in schizophrenia, independent of psychosis symptoms;^34^Trail Making Test: a neuropsychological test of visual attention and task switching that can provide information about visual search speed, scanning and speed of processing, mental flexibility, and executive functioning;^35^Food Craving Inventory: a 28-item self-reported measure of general and specific food cravings;^36^Alcohol Use Disorders Identification Test: a ten-item screening tool to assess alcohol consumption, behaviours, and problems associated with alcohol use;^37^Pittsburgh Sleep Quality Index: a 19-item self-reported measure of overall sleep quality assessing seven domains comprising subjective sleep quality, sleep latency, sleep duration, habitual sleep efficiency, sleep disturbances, use of sleeping medication and daytime dysfunction;^38^physical health measures including, BMI, waist circumference, waist-to-hip ratio, heart rate, blood pressure, HDL, LDL, triglycerides, total cholesterol, HbA1c, ELFTs, NAFLD and FIB-4.

### Other measures

In addition to the abovementioned measures, we will assess adherence to the trial investigational product. This will be based on self-report and capsule count at each visit. We will perform additional blood tests including a full blood count and measure clozapine/ norclozapine levels, as well as levels of CBD, THC and their metabolites.

Participants will also have the option of providing a saliva sample at baseline. This will be used to explore the presence of known genetic correlates of clozapine and obesity, including variants in genes such as *LEP* and *HTR2C*.^25^ The DNA samples collected in this study will be used to validate associations between DNA single-nucleotide polymorphisms and treatment-resistant clozapine patient populations.

Our research team has used this suite of measures in other clinical trials^39–41^ and found them to be acceptable to study participants with schizophrenia, with low rates of dropout due to burden of clinical measures.

### Statistical analysis

#### Sample size

A power analysis was conducted based on the mean difference in positive PANSS score between treatment arms at the primary analysis endpoint (12 weeks post-baseline assessment). A mean difference in positive PANSS score of 1.30 at 8 weeks^17^ (extrapolated to a conservative difference of −1.8 at 12 weeks, assuming a logarithmic trend over a linear trend), standard deviation difference of 3.739 (Cohen's *d* effect size of 0.48), correlation between assessment timepoints of 0.6, *α* = 0.025 (one-sided), and 1 − *β* = 0.8, with repeated measures (four assessment timepoints) and analysis of variance (ANOVA) as the planned analysis with pairwise contrast, yielded a requirement of 70 participants. Allowing for 20% dropout and rounding up to the nearest multiple of treatment arms (*n* = 2) suggests that a minimum sample of 88 participants is required overall.

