## Discussion

Schizophrenia remains one of the most complex and poorly understood psychiatric disorders. This trial seeks to generate new knowledge to support people with schizophrenia by determining the efficacy of add-on 1000 mg daily CBD for treatment of clozapine-resistant schizophrenia. Existing evidence suggests that CBD is well tolerated in this population with minimal side-effects.^42,43^

This trial has some limitations. First, there is no assurance that the study's findings will be generalisable to all individuals with clozapine-resistant schizophrenia. Although the proposed study is sufficiently powered to detect statistically significant differences between groups, the sample size (*n* = 88) is still small. Moreover, as the study sample is required to fulfil eligibility criteria such as abstinence from substances including amphetamine and cannabis, it may not be entirely representative of the real-world population.

This protocol provides a detailed account of the objectives, design, procedures and analytical approach of this trial. We anticipate that the results of the trial will show significant improvements in participants’ PANSS positive scores and will therefore inform clinical guidance on the maintenance treatment of clozapine-resistant schizophrenia. Moreover, we believe that this trial has the potential to minimise symptom severity and optimise quality of life for individuals with clozapine-resistant schizophrenia.

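### The sample size assumes one test at one-sided 0.025, but Table 2 tests four times at about 0.009: on the plan's own premise power with 70 completers is about 72%, not 80%

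*Protocol article*

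**What the plan says.** The Sample size section describes a fixed design. It takes a week-12 difference "extrapolated to a conservative difference of −1.8 at 12 weeks", a "standard deviation difference of 3.739", a Cohen's "d* effect size of 0.48" and a "correlation between assessment timepoints of 0.6". It tests with "α* = 0.025 (one-sided), and 1 − *β* = 0.8", "with repeated measures (four assessment timepoints) and analysis of variance (ANOVA) as the planned analysis with pairwise contrast", and this "yielded a requirement of 70 participants". The only step from there to 88 is a 20% dropout allowance and rounding to an even number.

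The Interim analysis section plans three looks, when 22, 44 and 66 participants have completed week 12. Table 2 labels these 25%, 50% and 75%, with 100% at n = 88. Its one-sided efficacy P-values are 0.0089, 0.0090, 0.0092 and 0.0094 (final). Its row for conditional power at the futility boundary ends at 0.80 in the n = 88 column. Interim results are described as non-binding.

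The Discussion states that "the proposed study is sufficiently powered to detect statistically significant differences between groups".

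**The concern.** The sample size rests on a critical value of 1.960 (one-sided 0.025), but the final analysis is to be judged at 2.349 (one-sided 0.0094). Spreading alpha almost evenly over four looks is legitimate, but it needs a larger maximum sample for the same power. The article applies no such increase. It also uses two different maxima for the amount of information: 70 evaluable participants in the Sample size section and 88 completers in Table 2.

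What is at stake is how the result will be read. If a true 1.8-point effect exists, the chance of missing it is larger than the stated 20%, and a null result would be weighed against power the trial does not have.

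**Working it through.** **Reproducing the stated figures.** 1.8/3.739 = 0.481, which agrees with d = 0.48. 70/0.8 = 87.5, so 88, which agrees.

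The 70 does not follow from the stated inputs. With (1.960 + 0.842)²/0.48² = 34.07, a plain two-arm comparison at week 12 needs 2 × 34.07 = 68.1 per arm, so 69 per arm and 138 in total. Using the correlation of 0.6:
- baseline-adjusted analysis, factor 1 − 0.36 = 0.64: 43.6 per arm, total 88;
- change score, factor 2 × (1 − 0.6) = 0.8: 54.5 per arm, total 110;
- mean of four visits, factor (1 + 3 × 0.6)/4 = 0.7: 47.7 per arm, total 96.

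At one-sided 0.025, the route found to give 70 is a one-sample formula applied to each arm (34.07, so 35 × 2). It ignores the comparison between arms. The steps below therefore take the plan's premise at face value: 70 completers give 80% at a single one-sided 0.025 test.

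**Inputs to the sequential check.**
- Drift for 70 completers: 1.960 + 0.842 = 2.802.
- Efficacy critical values from Table 2's P-values: 2.370, 2.366, 2.357, 2.349.
- Information fractions: 0.25, 0.50, 0.75, 1.
- Futility z-values from Table 2's δ rows. The standard error is the efficacy δ divided by its z: 15.64/2.370 = 6.60, 11.06/2.366 = 4.675, 8.99/2.357 = 3.813. The bounds are then −4.74/6.60 = −0.72, 3.53/4.675 = 0.755 and 6.10/3.813 = 1.60.

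Method: simulation of the four-look joint normal distribution, 2 million runs, Monte Carlo error about 0.0003.

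**Type I error.** With drift 0, the four thresholds spend 0.0251. The boundary is therefore a nearly flat, Pocock-like division of the same 0.025 used for the sample size. The article does not name the family, and nothing below depends on the name.

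**Power.** For N completers the drift is 2.802 × √(N/70); at N = 88 it is 3.141.

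| Completers | Efficacy bounds only | Futility bounds also followed |
|---|---|---|
| 70 | 72% | 69% |
| 84 | 80% | 77% |
| 88 | 82% | 79% |

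- The final test alone with 70 completers: Φ(2.802 − 2.349) = Φ(0.453) = 67%.
- If the looks fall at 22, 44, 66 and 70 completers (fractions 0.31, 0.63, 0.94 and 1), power is 72.5%, so the result does not depend on the spacing.
- To keep 80% with these boundaries and non-binding futility, the maximum must rise by a factor of about 1.19–1.20, to about 84 completers. At 20% dropout that is 84/0.8 = 105, so 106 randomised.

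**The two maxima.** Table 2's percentages are 22/88, 44/88 and 66/88, counted in completers. After the planned 20% loss there would be about 70 completers, so the third look would hold 66/70 = 94% of the completers rather than 75%, and the n = 88 column would not be reached.

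**O'Brien–Fleming comparison.** Critical values 2.024/√t at the same fractions correspond to one-sided P of about 0.00003, 0.0021, 0.0097 and 0.0215. Power at drift 2.802 is 79%, or 78.4% with looks at 22, 44, 66 and 70. The price is in early stopping: at the first look the chance of crossing under the planned effect is Φ(2.802 × 0.5 − 2.370) = Φ(−0.97) = 17% with Table 2's bound, and Φ(1.401 − 4.048) = 0.4% with this one.

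**The case against.** **Dropouts still contribute information.** The Data analysis section specifies a repeated-measures mixed model, a treatment-policy approach and multiple imputation, and participants who stop treatment may still be assessed. This stands. A reader might conclude that power is 72% or less, but 72% is not an upper limit: 70 effective completers give 72%, 76 give 76%, 79 give 78% and 88 give 82%. It remains the face-value figure, because 70 is the plan's own evaluable number.

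**Futility is non-binding.** This also stands. One might infer that a true effect would be missed 28–31% of the time, but the 31% applies only if the futility bounds are followed. As written, the figure with 70 completers is about 28%.

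**Table 2 shows 0.80 at 100%.** That entry is a conditional power on the futility row, not the overall power of the design. It is tempting to say that the sponsor counted the same 18 participants twice, once as dropouts and once as the inflation for the looks. The article does not show how 0.80 was obtained, and 88 completers give 82% or 79%, neither exactly 80%. What can be said is that the two sections use different maxima, and that the dropout allowance cannot also serve as the inflation.

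**The base figure is uncertain.** True. For a plain week-12 comparison with 70 participants, power is 52% at a single 0.025 test and 43% under Table 2. This does not remove the mismatch, but it makes 72% a conditional value.

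**It belongs in the analysis plan.** Details may. But alpha, power, sample size and boundaries are all stated in the article, and they do not fit together.

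**Conclusion.** The concern holds. The stated 80% belongs to a single test at one-sided 0.025, not to the four-look design in Table 2. Type I error is not in question.

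On the premise that 70 completers give 80% at a single test, power is about 72% with non-binding futility, a shortfall of about 8 percentage points. It is about 69% if futility is followed, and about 82% (79% with futility) only if nobody is lost. Partial data from dropouts would place it between the 70- and 88-completer values; how far depends on the timing of dropout and the correlation of visits, which the article does not settle. All of these figures would change if the base of 70 changes when it is re-derived.

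**What to change.** 1. Re-derive the base sample size from the stated effect, standard deviation, correlation and planned contrast, naming the formula, since 70 does not follow from them as written.
2. Replace the fixed-design calculation with one group-sequential calculation that states together the overall alpha, the boundaries, the maximum number of completers and the dropout inflation. Use the same maximum in the Sample size section and in Table 2, and recompute the information fractions from it.
3. Restate the power in the Sample size section and the Discussion. If Table 2's P-values and 70 completers are kept, this is about 72%, conditional on step 1.

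These steps cost a recalculation and revised wording; the downside is a less favourable stated power. No extra patients are required for the correction itself.

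Optional: if the sponsor wants to stay near the stated power with 88 randomised, O'Brien–Fleming-type boundaries would give about 79% on the same premise. They must be fixed before any unblinded interim look, and they lower the chance of stopping early for efficacy, most of all at the first two looks. Flat boundaries remain a legitimate choice, so this is a trade-off for the sponsor.

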There have been three randomised placebo-controlled trials, albeit not among people with clozapine-resistant schizophrenia.^16–18^ A 6-week double-blind parallel-group trial of 88 participants with partially responsive schizophrenia, not trialled on clozapine, compared adjunctive CBD 1000 mg/day with placebo.^17^ This study found significantly greater improvements in positive psychotic symptoms in the CBD group. However, it failed to reach significance with respect to the difference in the proportions of participants in the two groups showing ≥20% improvement in PANSS (Positive and Negative Syndrome Scale) total score. A second 4-week blind randomised controlled trial (RCT) among 42 participants receiving 600–800 mg CBD daily versus the standard antipsychotic medication, amisulpride, showed improvements in psychotic symptoms with both treatments and fewer adverse drug reactions in the CBD arm.^18^ However, the third study, a double-blind 6-week randomised controlled trial in 36 treatment-responsive patients with schizophrenia did not find a difference in psychotic symptoms between groups receiving adjunctive CBD 600 mg/day and placebo.^16^ Other non-randomised or single-dose CBD studies have shown equivocal results.^19^

CBD has been found to be well tolerated at different doses across several clinical trials. A trial by Taylor et al in healthy controls showed good tolerance of single CBD doses of 1500, 3000, 4500 and 6000 mg.^20^ In patients receiving multiple doses (750 and 1500 mg twice daily) for 6 days, CBD was also well tolerated, with no participants leaving the trial owing to adverse events.^20^ McGuire et al trialled doses of 1000 mg daily of CBD in patients with schizophrenia in addition to their usual antipsychotic medications for 6 weeks.^17^ Positive psychotic symptoms were lower in the treatment group, with similar adverse events to those of the placebo group, showing good tolerance for CBD.^17^

To date, there have been no trials of CBD among people with clozapine-resistant schizophrenia. This trial has the potential to identify CBD – if found to be effective – as a novel and safe adjunctive treatment for individuals with clozapine-resistant schizophrenia.

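### The stated 80% power from 70 evaluable participants in total is not reproduced for the week-12 between-arm contrast; on the plan's own inputs it is about 51% to 70%

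*Protocol article*

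**What the plan says.** The Sample size section of the protocol article bases the power analysis on the "mean difference in positive PANSS score between treatment arms at the primary analysis endpoint (12 weeks post-baseline assessment"). Its inputs are:

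- a difference of 1.30 taken from an earlier trial, "extrapolated to a conservative difference of −1.8 at 12 weeks";
- a "standard deviation difference of 3.739", giving d = 0.48;
- a correlation of 0.6 between timepoints;
- one-sided alpha of 0.025 and power of 0.8.

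These inputs, "with repeated measures (four assessment timepoints) and analysis of variance (ANOVA) as the planned analysis with pairwise contrast, yielded a requirement of 70 participants". Inflating that figure for an expected 20% loss "suggests that a minimum sample of 88 participants is required overall". The Abstract, Design and setting, and Participants sections all recruit 88 people in total, and allocation is 1:1.

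Table 1 schedules PANSS at weeks 0, 4, 8 and 12, so the four timepoints include baseline and three are post-baseline. The primary model under Data analysis has terms for arm, time, site and arm by time, and lists no baseline covariate. The Discussion says: "Although the proposed study is sufficiently powered to detect statistically significant differences between groups".

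The source of the effect is dated in two ways. The Sample size section has "A mean difference in positive PANSS score of 1.30 at 8 weeks". The introduction describes the same cited study as "A 6-week double-blind parallel-group trial of 88 participants with partially responsive schizophrenia".

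**The concern.** A standardised difference of 0.48 at a single visit is a moderate effect, and 35 evaluable people per arm is few for detecting it with 80% power. The stated correlation can help only if the analysis uses the baseline or other visits, and the article does not say how it entered the calculation.

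The stake is how a null result would be read. If true power is nearer one half to 0.7 than 0.8, a negative finding is weaker evidence against the target effect than the article implies. Readers, the DSMB and later meta-analysts would be relying on a power figure that the design does not have.

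**Working it through.** **Inputs.** d = 1.8/3.739 = 0.481 (stated as 0.48); rho = 0.6; one-sided alpha 0.025; power 0.80; 1:1 allocation; 20% dropout. All are from the Sample size section except allocation. Compound symmetry is assumed, so one correlation serves all pairs of visits.

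**Dropout step.** 70/0.8 = 87.5, rounded to 88. This reproduces. The issue is the 70.

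**Formula.** Normal approximation: n per arm = 2(1.960 + 0.842)² × f/d², where f is the variance of the analysed quantity relative to a single score. With f = 1 and d = 0.48 this is 68.1. The noncentral t adds one or two per arm and is used below.

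| Week-12 analysis | f | n per arm | Total evaluable | Power, 35 per arm | Power, 44 per arm |
|---|---|---|---|---|---|
| Unadjusted | 1 | 69–70 | 138–140 | 0.51 | 0.61 |
| Change from baseline | 2(1 − 0.6) = 0.80 | 56 | 112 | 0.60 | 0.70 |
| Baseline-adjusted | 1 − 0.6² = 0.64 | 45 | 90 | 0.70 | 0.80 |

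No row gives 70 in total. The mean of all four visits has f = (1 + 3 × 0.6)/4 = 0.70 and needs 49 per arm (98).

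**What does give 70.**

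- A two-sample t-test at d = 0.48 needs 70 *per arm* (69 with d = 0.481).
- Change averaged over four follow-ups has f = 0.70 + 1 − 1.2 = 0.50 and needs 35 to 36 per arm, about 70 in total. The trial has three follow-ups: f = 0.733 − 0.2 = 0.533, 37 to 38 per arm, 74 to 76 in total. Either way this is an average, not week 12.
- Adjusting week 12 for all three other visits has f = 1 − 3 × 0.36/2.2 = 0.509 and needs about 35 per arm, but it conditions on post-randomisation scores.

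**Partial data.** A mixed model that uses the scores dropouts gave before leaving has, with 88 randomised and 20% dropout, power of about 0.55 to 0.56 with baseline means free, or 0.71 to 0.73 with baseline means constrained equal.

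**Table 2.** Its one-sided efficacy P values correspond to z = 2.370, 2.366, 2.357 and 2.349. Scaling by the ratio of the futility to the efficacy delta gives futility z = −0.72, 0.76, 1.60 and 2.35 (for example, −4.74/15.64 × 2.370 = −0.72). Reading the futility row as one minus cumulative type II error, simulation gives:

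| Final drift | 25% | 50% | 75% | 100% |
|---|---|---|---|---|
| Table 2 as printed | 0.99 | 0.93 | 0.86 | 0.80 |
| 0.48 × √44 = 3.184 | 0.990 | 0.930 | 0.861 | 0.800 |
| 0.48 × √22 = 2.251 (88 in total, unadjusted) | 0.97 | 0.79 | 0.62 | 0.49 |

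The printed row needs (3.184/2.251)² = 2.0 times the information that 88 in total gives for the unadjusted contrast.

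**Interim penalty.** With the Table 2 efficacy boundaries and futility ignored (the interim results are non-binding), power at 70 completers is about 0.43 unadjusted and 0.62 baseline-adjusted. With all 88 observed it is 0.52 and 0.73.

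**Detectable difference.** At 35 per arm, 80% power needs d = 0.679 on the analysed scale: 0.679 × 3.739 = 2.5 points unadjusted, and 2.5 × 0.8 = 2.0 baseline-adjusted.

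**Extrapolation.** If the effect is proportional to ln(week), 1.30 × ln 12/ln 6 = 1.80 and 1.30 × ln 12/ln 8 = 1.55. With ln(1 + week) the results are 1.71 and 1.52.

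**The case against.** A reader might infer that 70 simply *is* the per-arm number and that 88 should have been too. The t-test match and Table 2 both invite this. The article does not establish it. It presents 70 as a total and lists a correlation and four timepoints, which a plain t-test would not use. An averaged change score with f = 0.50 also gives about 70 in total. It also yields the same drift, (0.48/√0.50) × √22 = 3.184, so Table 2 cannot separate the two explanations. The origin of the error is therefore open. That 70 fails for the week-12 contrast is not.

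A second tempting reading is that 88 participants give 51% power. That figure is for 70 completers, unadjusted. With full follow-up and baseline adjustment, power is about 0.80. This objection stands, and it is why a range is reported. The favourable end, however, needs no dropout, a baseline adjustment that the listed model terms do not include, and no interim penalty.

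Third, the meaning of the standard deviation input is unclear. If 3.739 is the SD of change scores, power at 70 completers is about 0.51 for change and 0.60 baseline-adjusted, which does not help the plan.

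Finally, one might conclude that the effect should be 1.55. The logarithmic formula is not given and the source is not at hand, so only the conflict between 6 and 8 weeks is established. A linear trend does not settle it: it would give 2.60 from week 6 or 1.95 from week 8, and 1.8 lies below both.

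**Conclusion.** The concern holds as a failure to reproduce the stated power. For the contrast that the Sample size section names, 70 evaluable participants in total give about 0.51 (unadjusted), 0.60 (change) or 0.70 (baseline-adjusted), and somewhat more than the first and last of these if the mixed model draws on dropouts' partial data. With the Table 2 efficacy boundaries, the unadjusted and adjusted figures fall to about 0.43 and 0.62. Only full observation of all 88 with baseline adjustment reaches 0.80, before any interim penalty. Table 2 likewise assumes about twice the information that 88 in total supply for the unadjusted contrast.

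These results rest on the plan's own d, correlation and alpha, on compound symmetry, and on 3.739 being the SD of a single score. The duration mismatch for the source trial is a separate, definite inconsistency; which figure is wrong cannot be decided from the article.

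**What to change.** 1. In the Sample size section, name the contrast and the variance model, say what the 3.739 is an SD of, and show how the correlation of 0.6 enters.
2. Restate power for 88 randomised in total, either as the range above or for the chosen model, including the interim boundaries. Give the difference detectable with 80% power: about 2.5 points unadjusted or 2.0 baseline-adjusted at 35 per arm.
3. Recompute the Table 2 futility row for the information that 88 in total provide under that model.
4. Amend the Discussion's statement on power to match.
5. Reconcile the 6-week and 8-week descriptions of the source trial and give the formula behind 1.8.

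Do not relabel 70 or 88 as per-arm. That would imply 176 randomised and contradict the Abstract, Design and setting, and Participants sections.

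The cost is a rerun of the calculation, some wording, and a less favourable stated power. An accurate statement needs no extra participants.
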